#### Safety

The proportions of children experiencing any side effect, as reported by the caregivers, will be compared between groups using the Mantel-Haenszel test, stratified by site. The analysis will evaluate the presence/absence of side effects, as an aggregate outcome variable.

#### Mechanism

To test for a difference in fecal secretory IgA the Wilcoxon rank-sum test will be performed. As this is a mechanistic outcome and the motivation of its study is distinct from other outcomes, the test will be performed at the 0.05 level. Data will be analyzed to determine if fecal secretory IgA levels 5 days and 4 weeks after initiation of treatment are higher among children treated with probiotic than those treated with placebo. Fecal sIgA data will also be analyzed by outcome, comparing levels among those with mild disease to those with moderate to severe disease.

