## Methods/Design

### Hypotheses

In children aged 3 to 48 months of age who present with less than 72 hours of AGE-like symptoms to an ED, the administration of a probiotic agent when compared with a placebo:

1. will result in a significantly lower proportion of children developing moderate to severe disease over the subsequent 2 weeks.

2. will not be associated with a significantly greater occurrence of minor side effects.

3. will be associated with a greater increase in secretory IgA (sIgA).

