#### Mechanism of action

In this group of patients, are fecal sIgA levels 5 days and 4 weeks after the initiation of treatment higher in those who receive Lacidofil compared to those who receive placebo?

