### Intervention

Informed consent will be obtained from each participant’s legally authorized guardian prior to enrollment into the study. Once consent is provided, the first dose will be administered in the ED. The sachet’s contents will be sprinkled into 30 mL of oral rehydration solution (ORS). Caregivers will receive instructions on study drug administration, completion of study forms, what and how much fluid to drink, criteria for seeing a health care practitioner or returning to the ED [see Additional file 1] and standardized AGE discharge instructions.

All patients will take one sachet every 12 hours for 5 days, at meal time, even once symptoms have resolved. The dose will be repeated once should vomiting occur within 15 minutes of medication administration. Children who are hospitalized will continue as per study protocol.

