### Randomization

#### Sequence generation

We used http://www.randomize.net to produce the study randomization lists stratified by site. The lists were sent to the central pharmacy at ACH where an independent research pharmacist prepared consecutively numbered kits according to the randomization schedule. The kits were couriered directly to the sites using insulated shipment containers and temperature monitors.

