#### Mechanism

To determine if probiotic administration increases fecal sIgA levels in children with AGE, the first stool sample produced following enrollment will be collected along with samples on Days 5 and 28. We will determine if fecal sIgA levels are greater among children treated with a probiotic agent compared with placebo. Levels will be correlated with clinical findings.

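### The sIgA comparison uses an unstratified rank test and applies one 0.05 level to two time points with neither named primary; it is valid but loses precision and leaves the error rate open

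*Protocol article*

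**What the plan says.** All references are to the protocol article.

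- **Test.** Statistical analysis, Mechanism: "To test for a difference in fecal secretory IgA the Wilcoxon rank-sum test will be performed". The level is 0.05, justified by the mechanistic nature of the outcome. The comparison is whether "fecal secretory IgA levels 5 days and 4 weeks after initiation of treatment are higher among children treated with probiotic". No stratification factor, covariate or primary time point is named.
- **Question and outcome.** The study question asks: "are fecal sIgA levels 5 days and 4 weeks after the initiation of treatment higher in those who receive Lacidofil". The Mechanism outcome agrees: "We will determine if fecal sIgA levels are greater among children treated with a probiotic agent compared with placebo". Only hypothesis 3 is worded as a change: the probiotic "will be associated with a greater increase in secretory IgA (sIgA".
- **Samples.** Outcomes, Mechanism: "the first stool sample produced following enrollment will be collected along with samples on Days 5 and 28". Under Stool sample testing, the Day 5 and Day 28 samples come from two of the five sites.
- **Dosing.** Intervention: "Once consent is provided, the first dose will be administered in the ED".
- **Design and the other tests.** Sequence generation says the randomization service was used "to produce the study randomization lists stratified by site". The Clinical and Safety analysis sections stratify the Wilcoxon test of the continuous severity score, the Van Elteren tests of the durations, and the Mantel-Haenszel tests.
- **Sample size.** Mechanism: difference 300 μg/g, SD 500 μg/g, 80% power, type I error 0.05, hence 45 per group. The plan is to recruit 100.

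**The concern.** Three features of the stated method do not fit the rest of the plan.

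1. **Site.** When randomization is stratified and the outcome differs between sites, an unstratified rank test counts the between-site spread as noise. A real effect becomes harder to detect, and the actual type I error falls below its nominal value.
2. **Time points.** The text speaks of one test at 0.05 but names two occasions. If a positive result at either would be reported as a mechanistic effect, the error rate for the sIgA question exceeds 5%. Holm's method is specified for the clinical secondary outcomes, but no rule covers the two sIgA tests.
3. **First stool and wording.** A first stool is collected and has no stated role in the comparison. Hypothesis 3 speaks of an increase and the analysis of levels. If that is left open, the choice between levels, a change score and an adjusted analysis could be made after the data are seen.

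At stake is how reliably one of the key outcomes can be answered. The primary clinical conclusion is not affected.

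**Working it through.** **Inputs from the article:** difference 300, SD 500, so d = 300/500 = 0.6; two-sided α = 0.05; power 80%; 45 per group required; 100 recruited, i.e. 50 per arm at 1:1; two sites; two time points.

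**Assumptions (the article gives no figures):** normal data; correlation r between first stool and follow-up; correlation between the Day 5 and Day 28 tests; site shift s in SD units; 25 children per arm at each site.

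**1. The plan's own figure.** n per arm = 2(1.960 + 0.842)²/0.6² = 43.6, so 44. The two-sample t-test gives 44.6, so 45. The stated figure reproduces. It is for one comparison of levels at one time point, at 0.05, with no baseline. At 50 per arm the t-test has 84.4% power.

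**2. Ignoring site.** Simulation with 6,000 trials per setting, d = 0.6, 50 per arm, plain Wilcoxon against Van Elteren:

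| Site shift s | Power, plain | Power, stratified | Type I, plain | Type I, stratified |
|---|---|---|---|---|
| 0 | 82.7% | 82.4% | 5.1% | 5.3% |
| 0.5 | 80.3% | 81.9% | 4.6% | 5.1% |
| 1 | 75.3% | 82.3% | 2.7% | 5.0% |

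The loss is about 0, 1.5 and 7 points. The plain test never exceeds its level beyond simulation error, and it becomes conservative as the sites diverge.

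**3. Two time points at 0.05 each.** If independent, 1 − 0.95² = 9.75%. With correlated test statistics, simulation gives 9.5% at 0.3, 9.1% at 0.5 and 8.4% at 0.7.

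Splitting α to 0.025 each would need 54.1, so 55 per arm by t-test, and leaves 76.4% power at 50 per arm. A fixed order keeps the first test at 0.05 and the 45 per group unchanged.

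**4. First stool as a covariate.** Adjustment reduces the SD to 500√(1 − r²), so the effect size becomes 0.6/√(1 − r²). t-test/ANCOVA power at 50 per arm:

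| r | Effect size | Power |
|---|---|---|
| 0 | 0.600 | 84% |
| 0.2 | 0.612 | 86% |
| 0.3 | 0.629 | 88% |
| 0.5 | 0.693 | 93% |

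**5. First stool in a raw change score.** The SD becomes 500√(2(1 − r)), so n per arm = 43.6 × 2(1 − r): 70 at r = 0.2, 62 at 0.3 and 44 at 0.5. It exceeds 50 per arm when 2(1 − r) > 50/43.6 = 1.147, i.e. when r is below about 0.43. Testing hypothesis 3 literally as a change score could therefore cost power, while covariate adjustment does not raise the required n at any r.

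**The case against.** A reader might infer from hypothesis 3 that the plan fails to test what it hypothesizes. The article does not support that. Randomization gives the arms equal expected sIgA at the start, so a difference in follow-up levels is, in expectation, the difference in change. The analysis also matches the study question, the Mechanism outcome and the sample size. Only the one-line hypothesis uses a different word.

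A reader might also infer that the first stool is thrown away. The section is merely silent about it. A condensed article can leave covariates to the full plan, so that silence is no error. Nor is this stool a clean baseline: it is produced after enrollment, and the first dose is given in the ED, so it may follow treatment. Adjustment is offered here as an inexpensive gain, and it is small if r is low.

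Two further defenses carry weight. Omitting site does not inflate type I error, and it costs almost nothing unless the sites differ appreciably. The outcome is mechanistic, and adoption rests on the primary clinical outcome, so an 8–10% error rate here does not change the trial's main conclusion.

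What remains is a method the article does state: a plain test where the plan's other tests are stratified, and one 0.05 level spread over two time points. The distinct motivation explains separating sIgA from the clinical outcomes. It does not explain two unadjusted tests within sIgA.

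**Conclusion.** The point holds as one of precision and of an unfixed error rate, not of invalidity.

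- **Site:** a power loss of about 0 to 7 points for site shifts of 0 to 1 SD, with a conservative test when sites differ. The shift and the equal split between sites are assumptions.
- **Multiplicity:** an 8–10% chance of at least one false positive across the two time points, if significance at either counts as a positive finding. The stated 45 per group covers one comparison only.
- **First stool:** a possible gain from about 84% to 86–93% power at 50 per arm for r of 0.2 to 0.5. The correlation is assumed, and these are t-test/ANCOVA figures under normality, not Wilcoxon figures.
- **Wording:** hypothesis 3 differs from the question, outcome and analysis sections and should be aligned with them.

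The change is worth making because sIgA is one of the three key outcomes and the remedy needs no new data.

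**What to change.** 1. Replace the plain Wilcoxon test with a site-stratified one: Van Elteren, as already used for the durations, or a site-stratified rank ANCOVA.
2. Use first-stool sIgA as a covariate, not in a raw change score. Define a collection window relative to the first dose, and state how missing first stools are handled. A log-scale ANCOVA or adding breast-feeding status is a matter of preference.
3. Before unblinding, name one time point as primary at 0.05 and test the other only if the first is significant, or apply Holm's method to the two. The article does not rank Day 5 against Day 28, so the choice belongs to the investigators.
4. Reword hypothesis 3 as a comparison of levels, in line with the study question, the Mechanism outcome and the analysis.

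The cost is wording, a little more analysis work, simple handling of missing first stools and a stricter rule for the second time point. No further samples or participants are needed under the fixed order.

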### Study questions

#### Clinical efficacy

Clinical efficacy will be determined as follows:

1. For previously healthy children, ages 3 to 48 months, who present with less than 72 hours of AGE-like symptoms to an ED, is the probability of developing moderate to severe disease (Modified Vesikari Scale (MVS) score ≥9) following ED evaluation, significantly different in those who receive Lacidofil compared to those who receive placebo?

2. Is there a difference in the (a) mean duration of diarrhea or (b) mean duration of vomiting?

3. Is there a difference in the probability of requiring an unscheduled healthcare provider visit?

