### Outcomes

#### Primary outcome (clinical)

The primary outcome is the development of moderate to severe disease in the 2 weeks after the index ED visit as measured by the MVS (Table 1) [44]. The original 20 point Vesikari Score, which has been employed as a dichotomous variable in many clinical studies [45-53], correlates with other meaningful measures such as caregiver anxiety, helplessness, stress, [54] parental worry, behavioral changes, and impact on the parents’ daily activities and distress [55]. However, percent dehydration, an element of the original score, is challenging to quantify due to difficulties in collecting follow-up weights, determining when rehydration has occurred, and the variation related to timing of voiding, stooling, eating, and drinking. Thus, this element is omitted or incorrectly assigned in many studies. The modified score includes an important and easy to obtain outcome that reflects global disease severity - need for unscheduled healthcare provider visits within 2 weeks of the index visit [44]. This is supported by evidence that the utilization of professional medical care correlates with disease severity [54].

**Table 1 T1:** Modified Vesikari Scale

**Points**	**0**	**1**	**2**	**3**
**Diarrhea duration**	0	1 to 96 hours	97 to 120 hours	≥121 hours
**Maximum number of diarrheal stools/24-hour period**	0	1 to 3	4 to 5	≥6
**Vomiting duration (d)**	0	1 to 24 hours	25 to 48 hours	≥49 hours
**Maximum number of vomiting episodes/24-hour period**	0	1	2 to 4	≥5
**Maximum recorded fever**	<37.0˚C R	37.1 to 38.4˚C R	38.5 to 38.9˚C R	≥39.0˚C R
**Future healthcare visit**	0%	-	Primary care	Emergency department
**Treatment**	None	Rehydration	Hospitalization	-

R, rectal.

Follow-up will occur daily until both the diarrhea and vomiting have resolved. On Day 14 each variable is assigned a score for the entire study period (Time 0 to Day 14); each patient gets a single total score for the study. Variables are scored based on the worst 24-hour period or on the total duration of symptoms or are based on the occurrence of an outcome.

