#### Mechanism

A study evaluating the impact of formula supplementation with oligosaccharides found fecal sIgA values of 729 and 377 μg/g in the intervention and control groups, respectively [68]. Assuming a clinically significant difference of 300 μg/g, a standard deviation of 500 μg/g, 80% power and a type I error of 0.05, the required sample size is 45 subjects/group. We will recruit 100 patients to provide multiple stool samples for this phase of the study.

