#### Clinical

The proportion of children with moderate to severe disease will be analyzed by utilizing a Mantel-Haenszel test, stratified by clinical center. Significance for the primary outcome measure will be determined using a two-sided 0.05 level. Secondary analyses of the primary outcome will employ logistic regression methods to adjust for covariates that may be imbalanced between groups. We will analyze the MVS as a continuous variable through a stratified Wilcoxon rank-sum test. The overall significance level for statistical tests on the secondary outcomes will be set at 0.05. Holm’s method will be used to adjust for multiple comparisons. The continuous variables of duration of diarrhea and vomiting will be measured in hours and analyzed with a Van Elteren test, stratified by clinical center. Unscheduled healthcare visits will be analyzed using a Mantel-Haenszel test, stratified by clinical center. The tertiary outcomes of the number of days the child is absent from daycare and the days the caregiver is absent from work will be analyzed using an appropriate model with robust estimates for standard errors. Dichotomous outcomes to be evaluated but unlikely to achieve significance include ED revisits, intravenous rehydration, and hospitalization. Additional analyses involving these outcomes will include linear and logistic regression models that adjust for possible effects of baseline characteristics.

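### The only specified analysis of sIgA against severity cuts the 0–20 MVS at 9 in about 100 children, although the full score is available and would usually be more powerful

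*Protocol article*

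**What the plan says.** All references are to the protocol article.

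- Statistical analysis, Mechanism: after the comparison of sIgA between arms, the plan adds "Fecal sIgA data will also be analyzed by outcome, comparing levels among those with mild disease to those with moderate to severe disease". Moderate to severe is defined under Clinical efficacy as "Modified Vesikari Scale (MVS) score ≥9".
- Outcomes, Mechanism: "Levels will be correlated with clinical findings". Neither a clinical measure nor a method is named.
- Primary outcome (clinical): "each patient gets a single total score for the study". The Table 1 item maxima add to 3+3+3+3+3+3+2 = 20.
- Statistical analysis, Clinical: "We will analyze the MVS as a continuous variable through a stratified Wilcoxon rank-sum test". This concerns the treatment comparison and not sIgA.
- Sample size estimates, Mechanism: the inputs are a difference of 300 μg/g, an SD of 500 μg/g, 80% power and alpha 0.05, and the plan arrives at 45 children per arm. On the number to be enrolled it says: "We will recruit 100 patients to provide multiple stool samples for this phase of the study". These figures are for probiotic versus placebo. No power or sample size is given for sIgA by severity.

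**The concern.** The one sIgA-by-severity analysis that is spelled out treats all scores from 0 to 8 as equal, and all scores of 9 or more as equal. The full score exists for every child, and the plan accepts it as a continuous variable elsewhere. The reasons given for a dichotomous score are mainly about a clinical endpoint: earlier use in trials, and a surveyed minimal important risk difference. They do not explain why a graded score should be cut when the question is its association with a graded biomarker.

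With about 20 children in the smaller group, a real but moderate link could easily be missed, and a null result could be misread as sIgA being unrelated to illness severity. In addition, the sentence mentions no adjustment for treatment, although the trial hypothesises that treatment lowers severity and raises sIgA.

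**Working it through.** **The plan's own figures reproduce.**
- sIgA by arm: n = 2(1.96 + 0.842)² × (500/300)² = 43.6, so 44 per group. The t-test version gives 44.6, so 45, as stated.
- Primary outcome, 25% versus 15% at 90% power: [1.96√(2×0.20×0.80) + 1.282√(0.25×0.75 + 0.15×0.85)]² / 0.10² ≈ 334.2, so 335 per arm and 670 in total, as stated. This confirms the planning rates as 25% and 15%.

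**Expected split.** With 1:1 allocation of 100 children, 50×0.25 + 50×0.15 = 12.5 + 7.5 = 20 are moderate-to-severe and 80 are mild. If the probiotic has no effect, the split is 25 and 75.

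**Information kept by the cut.** Under a bivariate normal model, a cut leaving a proportion p above it multiplies the correlation by φ(z_p)/√(p(1−p)). At p = 0.20 this is 0.280/0.400 = 0.70, so relative efficiency is 0.70² = 0.49. At p = 0.15 and 0.25 the efficiencies are 0.43 and 0.54.

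**Power by formula (Fisher z, n = 100).** The correlation that gives 80% power on the full score is 0.277. After the cut it becomes 0.277 × 0.70 = 0.194, and power is 49%, a loss of 31 points.

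**Power by simulation.** Settings: 2,000 runs per cell, an integer 0–20 score, Spearman on the full score against Wilcoxon rank-sum on the cut, two-sided 0.05, n = 100, 20% at or above 9. Losses are taken before rounding.

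| Assumed correlation | Full score | Cut at 9 | Loss (points) |
|---|---|---|---|
| 0.10 | 15% | 10% | 5 |
| 0.20 | 49% | 28% | 21 |
| 0.25 | 67% | 39% | 27 |
| 0.28 | 76% | 48% | 28 |
| 0.30 | 83% | 56% | 27 |
| 0.35 | 93% | 67% | 26 |
| 0.40 | 98% | 80% | 18 |
| 0.50 | 99.8% | 94% | 6 |

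For correlations of 0.20–0.35 the loss is 17–25 points with 25% above the cut, and 25–35 points with 15%. With n = 90 and 20% above the cut, the loss at a correlation of 0.50 is 7 points.

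**Using the plan's sIgA scale.** Assume that the severity groups differ by 300 μg/g with SD 500. Then d = 0.6, and the point-biserial correlation is 0.6×0.4/√(1 + 0.36×0.16) = 0.233. The underlying correlation is 0.233/0.70 = 0.33. Simulation (4,000 runs) gives:
- n = 100, 20% events: 64% with the cut, 91% with the full score
- n = 100, 15% events: 52% and 87%
- n = 100, 25% events: 69% and 91%
- n = 90, 20% events: 59% and 87%
- 200 μg/g, n = 100, 20% events: 34% and 57%

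**Treatment as a common cause, if the arms are pooled without adjustment.** Treated children would be 7.5/20 = 37.5% of the moderate-to-severe group and 42.5/80 = 53.1% of the mild group. A 300 μg/g treatment effect alone then makes sIgA 0.156 × 300 ≈ 47 μg/g lower in the moderate-to-severe group. The standard error is 500√(1/20 + 1/80) = 125, so the shift is 0.375 standard errors. The chance of rejection becomes 5.65% + 0.98% ≈ 6.6%, instead of 5%.

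**The case against.** The strongest reply is that a correlation is already planned. The Outcomes section promises "Levels will be correlated with clinical findings", and the word for an additional analysis in the Statistical analysis section suggests that the two-group comparison may come on top of it. This stands in part. A reader might infer that the plan has ruled out any use of the full score with sIgA, and the article does not support that. But the sentence names neither score nor method, so the cut remains the only severity analysis actually specified.

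Second, the cut answers a fair question: does sIgA differ between children with and without the trial's primary outcome? The article also reports that the cut-points tracked daycare and work absenteeism. This is a reason to keep the comparison, but it does not justify relying on it alone.

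Third, the size of the loss is not a figure in the document. This is correct. The 300 μg/g is stated for treatment arms, and the normal model is a simplification of a seven-item score with coarse steps. If sIgA changed as a pure step at 9, the full score would gain nothing.

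Fourth, a reader might infer that the trial's key mechanism outcome is underpowered. It is not implicated. The hypothesis, the study question and the sample size all concern sIgA by arm, and the stated sample size reproduces.

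Fifth, a reader might infer that treatment could manufacture the severity association. The article does not say that the arms are pooled unadjusted, and at the plan's own effects the artefact would be small.

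**Conclusion.** The point holds as an avoidable inefficiency in an exploratory analysis. It is not an error in a stated figure, and no efficacy conclusion depends on it. At the planning rates the comparison sets about 80 mild against 20 moderate-to-severe children and, under a smooth monotone relation, uses about half the available information. A single figure for the power loss would claim too much, because it depends on an unknown correlation: about 20–30 points for 0.20–0.35, and about 5–8 points at 0.10 or 0.50. The contrast of 64% with 91% rests on moving the plan's 300 μg/g and SD 500 from treatment arms to severity groups. Confounding by treatment is a minor additional reason to adjust. Priority is low.

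**What to change.** In Statistical analysis, Mechanism, replace the sentence on analysis by outcome with wording such as: The association of fecal sIgA at Day 5 and at Day 28 with disease severity will be analysed using the full MVS total (partial Spearman correlation, or regression of ranked or log sIgA on MVS), adjusted for treatment group and site; the comparison of mild with moderate-to-severe disease will be reported as a supporting result.

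This would also give the general statement under Outcomes, Mechanism, a named score and method. It costs one sentence and needs no new data, because each child already receives a total score. The downside is that a correlation or slope is a little less intuitive than a two-group difference, which is why that comparison is kept.

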#### Planned subgroup analyses

1. The presence of a MVS ≥9 will be analyzed by (i) age <1 year, (ii) breast-feeding status, (iii) antibiotic usage and (iv) protocol compliance.

2. Duration of vomiting will be analyzed only in those patients who have had ≥3 episodes of vomiting in the 24 hours prior to enrollment.

3. Daycare and work absenteeism will only be analyzed for children who attend daycare and caregivers who work.

4. In children with rotavirus infection, an interaction term will be added between treatment and rotavirus positivity in a logistic regression model. The independent variables in the model will be (i) treatment group, (ii) rotavirus positivity (yes/no) and (iii) the interaction between treatment group and rotavirus positivity.

5. Fecal sIgA levels will be subanalyzed based on the mother’s breast-feeding status.

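### The sIgA-by-severity comparison takes no account of treatment arm, so if the probiotic changes both sIgA and severity the contrast shows a link that exists in neither arm

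*Protocol article*

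**What the plan says.** Under Statistical analysis, Mechanism, the article plans a Wilcoxon rank-sum test for a difference in fecal sIgA and a comparison of Day 5 and Week 4 levels between arms. It then adds: "Fecal sIgA data will also be analyzed by outcome, comparing levels among those with mild disease to those with moderate to severe disease". Under Outcomes, Mechanism, the only other reference to this analysis is: "Levels will be correlated with clinical findings". Neither sentence mentions treatment arm, covariates, a time point or a test for the severity comparison.

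Three other places bear on it:

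- **Hypotheses.** The first is that the probiotic "will result in a significantly lower proportion of children developing moderate to severe disease over the subsequent 2 weeks". The third is that it produces a larger rise in sIgA than placebo.
- **Planned subgroup analyses, item 5.** "Fecal sIgA levels will be subanalyzed based on the mother’s breast-feeding status".
- **Planned subgroup analyses, item 1.** "The presence of a MVS ≥9 will be analyzed by (i) age <1 year, (ii) breast-feeding status, (iii) antibiotic usage and (iv) protocol compliance".

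Elsewhere the article does name strata or model terms. The primary outcome, symptom durations and unscheduled visits are stratified by center, side effects are stratified by site, and every term of the rotavirus interaction model is listed.

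**The concern.** Children in this comparison are grouped by something that happens after randomization, so the comparison is observational. Under the trial's own hypotheses, treatment arm is a common cause of the two quantities compared. The distortion therefore appears when the trial succeeds on both counts, which is when a reader would be most inclined to take an sIgA–severity difference as support for the mechanism. An effect of treatment on severity that bypasses sIgA would give the same picture. Evidence bearing on mechanism needs the association to hold within arm.

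Timing is a second, smaller matter. The Modified Vesikari Scale score covers Time 0 to Day 14, and one sIgA sample is taken on Day 28. The severity sentence does not say which sample it uses.

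**Working it through.** **Inputs from the protocol article**

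- sIgA difference 300 µg/g, SD 500 µg/g, 80% power, type I error 0.05, 45 per group, 100 children recruited (Sample size estimates, Mechanism).
- Control rate of moderate to severe disease 25%, absolute difference 10 points, hence 15% on probiotic (Sample size estimates, Clinical).
- 1:1 allocation (Allocation concealment), so about 50 per arm.

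**Reproducing the plan's figures.** For two means, n = 2(1.96 + 0.842)² × 500²/300² = 43.6, so 44 per group; the t-based version gives 44.6, so the stated 45 is reproduced. For 25% vs 15% at 90% power the calculation gives 335 per arm, which is the stated 670.

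**Spurious gap from arm, with no link within either arm**

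- Expected moderate-to-severe children: 50 × 0.25 + 50 × 0.15 = 20; mild: 80.
- Probiotic share of moderate-to-severe: 0.15/(0.25 + 0.15) = 37.5%.
- Probiotic share of mild: 0.85/(0.75 + 0.85) = 53.1%.
- Gap in mean sIgA: (0.531 − 0.375) × 300 = 46.9 µg/g, and 46.9/500 = 0.09 SD.

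**False-positive rate, normal approximation**

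- Variance, moderate-to-severe: 500² + 300² × 0.375 × 0.625 = 271,094.
- Variance, mild: 500² + 300² × 0.531 × 0.469 = 272,412.
- SE = √(271,094/20 + 272,412/80) = 130.2 µg/g.
- z = 46.9/130.2 = 0.36.
- Rejection probability = 1 − Φ(1.96 − 0.36) + Φ(−1.96 − 0.36) = 6.5%.

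**False-positive rate, Wilcoxon simulation** (10,000 runs, 50 per arm, no within-arm link)

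| Scenario | Arms together | Stratified by arm (Van Elteren) |
|---|---|---|
| 25% vs 15%, normal sIgA | 6.1% | 4.9% |
| 25% vs 15%, log-normal sIgA (means 377 and 677, SD 500) | 8.9% | 4.8% |
| 25% vs 25%, normal sIgA | 5.1% | 5.2% |

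The last row shows that a treatment effect on sIgA alone does no harm: if treatment does not change severity, the gap is zero.

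**Breast-feeding (assumed values; none are in the document).** Take an overall event rate of 20%, prevalence 20–50%, an sIgA shift of 200–1000 µg/g and a relative risk of moderate to severe disease of 0.5–1.0. At the upper end (50%, 1000 µg/g, 0.5), the risk is 0.20/(0.5 × 0.5 + 0.5) = 26.7% in non-breast-fed and 13.3% in breast-fed children. The breast-fed share is then 0.5 × 0.133/0.20 = 33.3% of moderate-to-severe and 0.5 × 0.867/0.80 = 54.2% of mild. The gap is 0.208 × 1000 = 208 µg/g, with a rejection rate of 23%. At a relative risk of 1.0 the gap is 0 and the rate 5%. The answer is set by the assumptions, so no size can be claimed for this source.

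**The case against.** The strongest objection is that the article is silent on arm, not wrong about it. A reader might infer that the plan has decided to pool the arms; it says no such thing. This is one exploratory sentence in a condensed article, and covariates are commonly left to the full protocol or SAP. That stands as a limit on the finding. What remains is that the sentence defines its two groups by severity only, in an article that names strata or terms for most other analyses. Followed as written, it is an unstratified contrast.

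Three stronger readings are tempting and are not supported:

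- **That breast-feeding is ignored.** Item 5 of the subgroup list plans an sIgA subanalysis by breast-feeding status. It is simply not tied to the severity comparison. Age is not mentioned for sIgA at all. Item 1 lists subgroups for the severity outcome; that does not assert that breast-feeding or age changes the risk.
- **That a treatment effect on sIgA, or breast-feeding, is enough by itself.** Each must relate to both sIgA and severity.
- **That the false-positive rate is badly inflated.** Combining arm with a 1.5 SD breast-feeding shift at 40% prevalence can give a gap of 0.37 SD and, with an SE of 0.25 SD, a rate of about 32%. That SE leaves out the extra spread the shift itself creates. With an SE of about 0.32 SD the rate is about 21%, and the inputs are still not the document's.

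It is also fair to say that the article makes no causal or mediation claim from this contrast, and that the mechanism question is answered by the randomized comparison of arms, which is unaffected.

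**Conclusion.** The point holds as a small improvement to an exploratory analysis. Under the protocol's own planning effects, and assuming the 300 µg/g difference applies at the time point analysed, a severity contrast that disregards arm shows about 47 µg/g (0.09 SD) with no within-arm link. Its false-positive rate is about 6–9% instead of 5%. Stratifying by arm brings it back to about 5%. The distortion vanishes if treatment leaves either sIgA or severity unchanged. Any contribution from breast-feeding or age is possible but cannot be sized from the document.

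**What to change.** State that the severity comparison is made within arm. Either of these would do:

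- a Van Elteren test stratified by treatment arm, a method the article already uses for symptom durations; or
- a regression of log sIgA on severity with treatment group in the model, and age and breast-feeding status as covariates.

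Bring in age and breast-feeding as covariates and not as further strata. Only about 20 moderate-to-severe children are expected, of whom 50 × 0.15 = 7.5 are on probiotic. At an assumed 40% breast-fed, that leaves about 0.4 × 7.5 = 3 in the breast-fed probiotic cell, and fewer if breast-feeding is protective.

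Name the sample used, label the comparison exploratory, and say that Day 28 sIgA, measured after the Day 14 score, will not be read as a cause of severity.

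The cost is a change of wording and a few degrees of freedom in about 100 children. The article already plans to analyse by age and breast-feeding status, so no new data are needed. No sample size, power or primary inference changes.
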